#### Control group

Mindset will be compared to an active control condition to control for attention. The control group also begins with a session zero to formulate their educational goals and will receive twelve weekly assignments via e-mail, without any face-to-face contact involved. The home assignments will take about 1 h to complete. No feedback will be provided on these assignments. The topics of the assignments are designed in such a way that they do not focus on cognitive functions but still provide some educational support. Examples of the exercises are “requesting for support,” “dealing with stress,” and “responding to feedback.”

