### Interventions

#### CR training

The Mindset training is designed to improve the cognitive abilities of students with psychiatric disorders, including psychotic disorders, and is aimed at improving academic outcomes. The training consists of twelve individual, 1-h meetings spread over 12 weeks. Personal educational goals of the participants will be formulated during an introductory meeting (session zero). The students will be asked to relate the skills and strategies practiced during the training to their own educational goals. During the training, four cognitive domains will be targeted: (1) prospective memory, (2) attention and concentration, (3) verbal learning and memory, and (4) cognitive flexibility and problem-solving. All sessions follow the same structure: review of last session’s home exercises, overview and importance of the current session’s topic, practice exercises, and review of new home exercises. The training includes practical strategies such as agenda usage and paying attention during class, forming a direct link to educational settings. The trainers are professionals from the participating MHC services and received a 4-day training in the CR by the developer of the original CR training.

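### The control is said to control for attention but has no trainer contact or feedback after session zero, so exploratory between-arm estimates cannot separate CR content from about 12 hours of contact

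*Protocol article*

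**What the plan says.** All references are to the protocol article.

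- **Purpose of the comparator** (Control group): "Mindset will be compared to an active control condition to control for attention".
- **What the control arm receives** (Control group): a session zero to set educational goals, then "twelve weekly assignments via e-mail, without any face-to-face contact involved". On duration: "The home assignments will take about 1 h to complete". On response from staff: "No feedback will be provided on these assignments". The topics are educational but deliberately not cognitive. Study procedures confirms that these assignments come with no extra support.
- **What the CR arm receives** (CR training): also a session zero on personal educational goals. Then: "The training consists of twelve individual, 1-h meetings spread over 12 weeks". Each session includes "review of last session’s home exercises, overview and importance of the current session’s topic, practice exercises, and review of new home exercises". The trainers are professionals from the participating services who had four days of training in the method.
- **What the comparison is used for**: Exploratory outcome measures says that school and cognitive functioning are collected for an early view of efficacy. Proposed analyses compares the quantitative outcomes from T0 to T2 to estimate potential treatment effects, and disclaims hypothesis testing. The main outcomes are feasibility and applicability.

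**The concern.** When a comparator is said to control for attention, the usual meaning is that both arms receive similar contact with, and interest from, a provider. A difference between arms can then be credited to the specific content of the intervention. The details printed beside the claim show that this balance is absent after session zero: one arm sees a trainer individually every week and has its homework reviewed, while the other receives e-mails and no response.

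What is at stake is how the exploratory estimates are read. The Discussion presents the trial as groundwork for further research on CR in education. If a between-arm difference is taken as adjusted for attention, a later trial could be planned on an effect credited to CR content that partly or wholly reflects individual contact. Five of the exploratory scores are self-reports (EBQ, MSLSS school subscale, CSEI, and the two CPSA totals), and these are likely to be more exposed than the CANTAB tests. The Discussion does not mention the imbalance as a limitation.

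**Working it through.** The protocol article gives no contact-time figure of its own, so there is none to reproduce. The check compares the two intervention descriptions feature by feature.

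| Feature | CR arm (CR training) | Control arm (Control group, Study procedures) | Matched? |
|---|---|---|---|
| Session zero with goal setting | Yes | Yes | Yes |
| Number and rhythm of units | 12, over 12 weeks | 12, weekly | Yes |
| Nominal time per unit | 1 h meeting | About 1 h assignment | Nominally |
| Trainer contact after session zero | Individual, every unit | None | No |
| Feedback on work | Home exercises reviewed in each session | None | No |

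**Scheduled trainer contact after session zero** = number of units × contact hours per unit.

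- CR: 12 × 1 h = 12 h
- Control: 12 × 0 h = 0 h
- Difference: 12 h

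These are scheduled hours; attended hours may be fewer.

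**Nominal task time.**

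- Control: 12 × about 1 h = about 12 h, reading the stated hour as per assignment.
- CR: 12 × 1 h = 12 h of meetings, plus home exercises whose length is not given.

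The scheduled units therefore match, but total time is not shown to be equal.

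**What the imbalance does to an estimate.** If a specific CR effect S and a contact effect A add together, the between-arm difference estimates S + A. Nothing in the design varies contact separately from content, so S and A cannot be separated. A larger sample would narrow the interval around S + A but would not separate the two.

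**Illustration of scale.** The protocol article gives no size for A, so the following rests on an assumption. Take 30 per arm and a simple standardised comparison of two means; the planned repeated-measures analysis would differ somewhat.

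- 95% half-width = 1.96 × √(2/30) = 0.51 SD.
- Assume S = 0. With A = 0.2 SD, the interval would exclude zero in favour of CR about 12% of the time. With A = 0.5 SD, it would do so about 49% of the time.
- In each case the estimate is shifted from S by the whole of A.

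**The case against.** The strongest reply is that this is a feasibility pilot comparing a whole package with a lighter alternative, which is a legitimate choice. The control is not inert: it shares session zero, the weekly rhythm, nominal task time and educational engagement with the CR arm. The lack of contact and feedback is stated openly. Hypothesis testing is disclaimed, and nowhere does the article promise to credit a difference to CR content separately from its delivery. Assessors are blinded. Participants would also know their arm under a contact-matched control, so reliance on self-report is partly a separate matter.

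Most of this stands and limits the point. It does not rescue the sentence on attention, which is an affirmative claim about the comparator that its own section contradicts. Blinded assessors do not balance contact.

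A reader might infer more, but the document does not support these stronger readings:

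- **That the feasibility findings are confounded too.** Trainer forms, interviews, dropouts, and eligibility and recruitment rates are not defined as between-arm contrasts. No comparison of dropout by arm is specified, and any influence of trainer meetings on retention is part of the package whose feasibility is being studied.
- **That the trial cannot know whether control participants did the assignments.** The article is condensed, and its full list of measurements is in a figure that is not shown. Interviews at T1 are held with participants and are not said to be limited to the CR arm. Silence here is not evidence of absence.
- **That an attention effect has been shown.** It has not. The point is that such an effect, if present, could not be told apart from a specific one.

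**Conclusion.** The statement that the comparator controls for attention is wrong as written. The control matches session zero, weekly schedule and nominal task time of about 1 h per unit. It leaves a difference of 12 h versus 0 h in scheduled trainer contact after session zero, and it offers no feedback where the CR arm has regular review.

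The consequence is confined to the exploratory between-arm estimates. These estimate Mindset with its trainer contact against unsupported assignments, and cannot be apportioned between content and contact. The conclusion rests on the schedule as described and on reading attention in its ordinary sense of provider contact. It does not depend on the assumed 0.2 to 0.5 SD, which only shows scale. The feasibility aim is unaffected.

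**What to change.** 1. In the Control group section, replace the phrase about attention with wording such as: the control condition matches the CR training on educational task time and weekly schedule, but not on trainer contact or feedback.
2. In Proposed analyses and in the Discussion, state that between-arm estimates on the exploratory outcomes reflect Mindset including individual trainer contact versus unsupported assignments, and will not be attributed to CR content alone.

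Neither intervention, the measurements nor the sample size changes. The cost is a few sentences and a more modest efficacy claim.

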### Measurements

A full list of measurements and measure points is given in the SPIRIT flow diagram (Fig. 1).

At baseline, the following demographic information will be collected per participant: age, gender, alcohol and drug usage, cultural background, education (previous and current), level of education, number of hours spent on their education per week (i.e., school credit hours and homework), living arrangements (living with parents/roommate(s)/partner and/or having children), employment information (number of hours), diagnosis (including age of onset and symptom severity), and medication use (name and frequency).

#### Feasibility, applicability, and fidelity outcome measures

The main study outcomes are study feasibility and applicability and will be measured using an evaluation form completed by the trainers, an interview with trainers and participants, and by examining study dropouts. In addition, patient eligibility and recruitment rates will be included as a measurement for feasibility and applicability of the training within this population as the number of potentially eligible people compared to the number of actual participants.

Training fidelity will be measured by the previously described interview and a session evaluation form, which contains a short checklist of all session components. The evaluation forms are designed in such a way that the trainer can provide information on how much of the sessions they have covered per exercise. The form also allows the trainer to provide feedback for each exercise within the session, as well as general feedback about the session. The fidelity measurements will provide greater understanding and description of how the training criteria have been attained, or why they may not have been attained.

The evaluation interviews will be semi-structured, audio-recorded (with consent), and transcribed. During the interview, questions like “Which session did you find most useful?” and “Are there aspects of the training that can be, or need to be, improved?” will be asked. All interviews will be encoded by two independent researchers. The codes obtained from both researchers will be compared and discussed, resulting in one coding file for each of the interviews.

#### Exploratory outcome measures

School- and cognitive functioning will be measured as exploratory outcomes to get a first impression of the efficacy of Mindset. To do this, objective and subjective school functioning, school satisfaction, school self-efficacy, subjective school functioning, strategy use, and cognitive functioning will be collected. In addition, information concerning interruptions in schooling (like school dropouts) will be gathered during the interviews.

#### Objective school functioning

School performance will be calculated as percentage of courses successfully completed using the following formula: $$ \frac{\mathrm{succesfully}\ \mathrm{completed}\ \mathrm{courses}}{\mathrm{number}\ \mathrm{of}\ \mathrm{courses}}\times 100\% $$, because the number of courses will not be the same for all participants. Therefore, an absolute number will not provide enough information about the total performance per student.

#### School satisfaction

School satisfaction will be measured using the Multidimensional Students’ Life Satisfaction Scale (MSLSS)—school subscale [46]. This subscale consists of nine statements about school satisfaction, for example, “I look forward to going to school” and “There are many things about school I don’t like.” Respondents are asked to indicate on a 4-point scale ranging from 1 (rarely) to 4 (always) to what extent the statements are applicable to them. Negative items like “I wish I didn’t have to go to school” will be reverse-scored. Higher scores indicate higher levels of school satisfaction.

#### School efficacy

School efficacy will be measured using the College Self-Efficacy Inventory or CSEI [47]. The CSEI is a 22-item self-reported questionnaire measuring student confidence levels related to their use of post-secondary educational skills such as “write a course paper” and “ask a professor or instructor a question outside of class.” The CSEI uses a 9-point scale, ranging from 0 (totally unconfident) to 8 (totally confident). Total scores will be used for analyses, where higher scores indicate higher confidence levels throughout the scale.

#### Strategy use and cognitive functioning

Strategy use and subjective cognitive functioning will be measured using the Cognitive Problems and Strategies Assessment, or CPSA [32]. This questionnaire contains 35 cognitive problems, such as “I have difficulty remembering to do things that I have scheduled” and 30 strategies like “I keep a written list of things I need to do.” The CPSA uses a 4-point scale ranging from 0 (rarely/never) to 3 (always). Total scores on “cognitive problems” and on “strategy use” will be calculated and used for analysis separately. Higher scores on “cognitive problems” indicate having more problems, and higher scores on “strategy use” indicate using more strategies.

#### Cognitive functioning

Objective cognitive functioning will be measured using the Cambridge Neuropsychological Test Automated Battery or CANTAB [48]. The CANTAB includes seven different modules measuring various neurocognitive functions and processes, including working memory, episodic memory, executive function, emotion recognition, cognitive flexibility, processing speed, and sustained attention.

### Randomization and blinding procedures

Randomization will be done in blocks of four and six participants, stratified for gender to control for possible gender effects [25]. Participants will be randomly assigned to either the CR or control condition by an independent researcher. Assessments will be done by trained bachelor or master level students in Psychology or Nursing, supervised by senior psychologists. The assessors are blinded to the conditions of the participants.

### Handling and storage of data and documents

Data will be handled confidentially in compliance with the Dutch Personal Data Protection Act (*Wet Bescherming Persoonsgegevens*; WBP). Research assistants will assign each participant with a unique identification code. The key to this code and a subject identification list will be safeguarded by the project manager. All data will be stored and locked at the Hanze University of Applied Sciences Groningen. Raw research data will be stored until 15 years after finishing the study and will be destroyed thereafter according to the code of proper use (“Gedragscode Gezondheidsonderzoek”; www.fmwv.nl).

### Dissemination

Dissemination of the results of the project will take place through scientific publication(s) in (inter)national peer-reviewed journals; presentations and workshops during national and international conferences of associations of educational staff, mental health workers, and rehabilitation specialists; a closing symposium; online introductory course on Supported Education for mental health professionals, students, and educational professionals; newsletters; and social media (LinkedIn groups, Twitter, Facebook, etc.).

### Proposed analyses

Analyses will be performed according to the “intention to treat” (ITT) principle. Descriptive statistics will be provided for all normally distributed variables in the form of mean scores and standard deviations for each of the assessment instruments. Descriptive statistics of variables that are not normally distributed will be represented as median scores and ranges. Data from the interviews will be qualitatively analyzed. Differences in the quantitative outcomes will be examined for T0 to T2 using repeated measures of variance with the MANOVA test using 95% confidence levels providing estimates of potential treatment effects since real significance and hypothesis testing is not applicable for a pilot study.

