**Methods/design:**

Sixty students diagnosed with a psychotic disorder and currently reporting cognitive deficits will be included from four Dutch Mental Health Care institutes. Half of the participants (*N* = 30) will be randomly assigned to the CR training consisting of twelve, individual, weekly 1-h meetings. The other half will be assigned to an active control condition consisting of twelve weekly assignments that will be sent by email aiming to improve school performance. Students will be evaluated at baseline (T0), directly after finishing the CR training or control intervention (T1), and 6 months later (T2). Treatment feasibility will be the primary outcome, using evaluation forms, interviews with trainers and participants, number of study drop outs, and patient eligibility and recruitment rates. School functioning, cognitive functioning, and strategy use will also be assessed to get a preliminary idea of the potential effectiveness of the intervention.

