### Sample size calculation

Sample size calculations are not applicable since the study focuses on the feasibility and applicability of the cognitive remediation training. According to the literature, a sample size of 25 to 30 per group should be sufficient to estimate moderate effect sizes in a pilot test for adequacy and acceptability of the instruments using *α* = 0.5 [43, 44]. We therefore aim for 30 participants per group. Participants will be recruited from the four participating sites providing variation in demographic and clinical characteristics useful for conclusions on general feasibility.

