**Fig. 1 Fig1:**
[figure not shown]
SPIRIT flow diagram of the study procedure showing enrolment, interventions, and assessments

Feasibility, applicability, and exploratory efficacy outcomes will be assessed at baseline (T0), upon completion of the CR training or control intervention (post-treatment; T1), and 6 months after T1 (follow-up; T2). The written evaluation forms for fidelity and feasibility will be completed by the trainers after each session. Evaluation interviews will be held at the end of the training (T1) with both participants and trainers and will be performed by the researcher involved.

Half of the participants will receive the CR training (intervention group), whereas the other half will receive study assignments without additional support (control group). Participants in the control group are offered Mindset 1 year after the experimental group completes the intervention. Participants will receive compensation (three times gift coupons of 12.50 euro each) for filling in the questionnaires at baseline (T0), post-treatment (T1), and during the follow-up, 6 months after T1 (T2).

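### The plan disclaims hypothesis testing and promises effect estimates, but its only named method is a MANOVA test with T0 among the outcomes; T0-adjusted differences with intervals would fit the aim better and be more precise

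*Protocol article*

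**What the plan says.** The Proposed analyses section of the protocol article covers all quantitative outcomes in one sentence. It begins "Differences in the quantitative outcomes will be examined for T0 to T2 using repeated measures of variance with the MANOVA test" and continues by describing the purpose as "95% confidence levels providing estimates of potential treatment effects since real significance and hypothesis testing is not applicable for a pilot study". No other method for comparing the arms is named. The section specifies no between-arm contrast, no time point for one and no adjustment for the baseline value.

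Other sections give the context:
- **Study procedures:** T0 is the baseline assessment, T1 falls at the end of training or control, and T2 six months after T1.
- **Exploratory outcome measures:** school and cognitive functioning are exploratory and serve as an early look at efficacy. The main outcomes, described in the section before, are feasibility and applicability.
- **Sample size calculation:** "We therefore aim for 30 participants per group". This rests on a rule taken from the literature, not on a power or precision calculation.
- **Randomization and blinding procedures:** randomisation is stratified by gender.

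**The concern.** There are two related problems.

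**Aim and method do not match.** The sentence sets testing aside and asks for estimates, yet the procedure it names is a test. With three visits and two arms, the MANOVA test of whether the arms differ over time has 2 degrees of freedom. It yields a statistic and a p-value, which show neither the size nor the direction of a difference nor the visit at which it occurs. The 95% confidence level has no defined quantity to attach to. A reader of the results could be left with the kind of result the plan sets aside and without the kind it promises.

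**T0 is used inefficiently.** No treatment effect can exist at baseline, so T0 is best used to explain variation in the later scores. Placing it among the responses makes the natural treatment contrast a difference between arms in change from T0. With 30 per arm the intervals are already wide, and this choice widens them further for no gain.

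At stake are the usefulness and precision of the exploratory effect estimates, which the Discussion section expects to serve as groundwork for later research.

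**Working it through.** **Inputs**
- n = 30 per arm, from Sample size calculation. The total is 2 × 30 = 60, which agrees with the stated total. The article gives no precision or power figure to reproduce.
- Visits T0, T1 and T2, from Study procedures.
- Assumed, because the article does not state them: outcome SD = 1 at every visit and in both arms, and correlation ρ between T0 and the later score from 0.3 to 0.8. Full follow-up is also assumed.

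**Step 1: variance per participant**
- Change from T0: 1 + 1 − 2ρ = 2(1 − ρ).
- Conditional on T0: 1 − ρ².
- Ratio, adjusted to change: (1 − ρ²) / [2(1 − ρ)] = (1 + ρ)/2, which is below 1 for every ρ below 1.

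The ratio is 0.65, 0.75, 0.85 and 0.90 at ρ = 0.3, 0.5, 0.7 and 0.8. Adjustment therefore saves 35%, 25%, 15% and 10% of the variance.

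**Step 2: 95% interval half-width for the between-arm difference**
- Change contrast: t(58) × √[2(1 − ρ) × 2/n].
- Adjusted contrast: t(57) × √[(1 − ρ²) × 2/n] × √[1 + 1/(2n − 4)]. The last factor allows for estimating the T0 slope.

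At ρ = 0.5, the change contrast has standard error √(1 × 2/30) = 0.258 and half-width 0.517. The adjusted contrast has standard error √(0.75 × 2/30) × √(1 + 1/56) = 0.226 and half-width 0.452. The ratio is 1.144.

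| ρ (assumed) | Change contrast | T0-adjusted | Change interval wider by |
|---|---|---|---|
| 0.3 | 0.612 | 0.498 | 23% |
| 0.5 | 0.517 | 0.452 | 14% |
| 0.7 | 0.400 | 0.373 | 7% |
| 0.8 | 0.327 | 0.313 | 4% |

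Half-widths are in SD units. Percentages are from unrounded values. An analysis that ignores T0 altogether has half-width 0.517, so below ρ = 0.5 the change contrast is less precise than not using the baseline at all.

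**Step 3: check by simulation**

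For each ρ, 4,000 trials were simulated with 30 per arm, a true difference of 0.5 SD at T1 and T2, and the same correlation between all visits. The contrasts were evaluated at T2. Mean half-widths, change against adjusted, were:
- ρ = 0.3: 0.607 and 0.495
- ρ = 0.5: 0.514 and 0.449
- ρ = 0.7: 0.398 and 0.370
- ρ = 0.8: 0.326 and 0.312

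Both estimators averaged 0.50 to 0.51, so the loss is in precision and not in bias.

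**The case against.** The strongest reply is that a repeated-measures MANOVA is a fitted linear model. Arm-by-visit means, between-arm contrasts and their intervals can all be taken from the same fit. The sentence mentions 95% confidence and estimates, and commits to no p-value or threshold. On this reading the plan is merely brief, and a journal article may leave the detail to a fuller document. The preference for baseline adjustment would then be a matter of efficiency, on outcomes that decide nothing.

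Much of this stands. A reader might infer that the named method cannot produce treatment-effect estimates, and the article does not support that: the estimates are obtainable but undefined. Nor does it support reading the sentence as a commitment to declare significance. A repeated-measures model that holds the T0 means equal across arms would recover about the precision of adjustment, although an ordinary MANOVA does not impose this. The saving expressed as participants also has little force, because the sample size was not derived from a precision target.

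The reply does not remove the point. The article does not simply omit a method. It names one, "using repeated measures of variance with the MANOVA test", and that method's direct result is of the kind the sentence sets aside. A method that matches the stated aim and is more precise can be run on data already being collected.

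**Conclusion.** The point holds as a mismatch between aim and named method, together with an avoidable loss of precision. At 30 per arm the change-type contrast has a 95% interval about 4% wider at ρ = 0.8, 7% at 0.7, 14% at 0.5 and 23% at 0.3. The loss is therefore modest if the scales are highly stable over time and more noticeable if they are not. The figures assume equal variances and full follow-up, and every value of ρ is an assumption.

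Two stronger inferences are not supported. The estimates would not be biased, since under randomisation both contrasts target the same effect. The trial's main conclusions are not at risk either, since feasibility and applicability are judged from evaluation forms, interviews, dropout and recruitment, and do not depend on this analysis. The change is worth making because it is free, but the consequence of leaving the text as it stands is limited to the exploratory outcomes.

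**What to change.** In Proposed analyses, replace the MANOVA test. For each quantitative exploratory outcome measured at T0, report the adjusted mean difference (CR minus control) at T1 and at T2, each with a 95% confidence interval. Take both from one repeated-measures model of the T1 and T2 values, with the T0 value and gender (the stratification factor) as covariates and terms for arm, visit and arm-by-visit. State that the results are reported as estimates, without significance tests.

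The cost is a change of analysis wording. No new data, visits or participants are needed.
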